## Abstract

**Background:**

Older adults often experience physical, sensory, and cognitive decline. Therefore, they have a high risk of falls, which leads to severe health and psychological consequences and can induce fear of falling. Rehabilitation programs using exergames to prevent falls are being increasingly studied. Medimoov is a movement-based patient-personalized exergame for rehabilitation in older adults. A preliminary study showed that its use may influence functional ability and motivation. Most existing studies that evaluate the use of exergames do not involve an appropriate control group and do not focus on patient-personalized exergames.

**Objective:**

This study aims to evaluate the effects of Medimoov on risk of falls and fear of falling in older adults compared with standard psychomotor rehabilitation.

**Methods:**

This is a serial, comparative, randomized controlled group study. Both groups (n=25 in each) will receive psychomotor rehabilitation care. However, the methods of delivery will be different; one group will be exposed to the Medimoov exergame platform, and the other only to traditional means of psychomotor rehabilitation. The selection criteria will be (1) age of 65 years or older, (2) ability to answer a questionnaire, (3) ability to stand in a bipedal position for at least 1 minute, (4) score of 13 or greater on the Short Fall Efficacy Scale, and (5) stable medical condition. An evaluation will be made prior to starting the intervention, after 4 weeks of intervention, and at the end of the intervention (after 8 weeks), and it will focus on (1) risk of falls, (2) fear of falling, and (3) cognitive evaluations. Physical activity outside the session will also be assessed by actimetry. The outcome assessment will be performed according to intention-to-treat analysis.

**Results:**

The protocol (2019-11-22) has been approved by the Comité de Protection des Personnes Nord-Ouest I–Université de Rouen (2019-A00395-52), which is part of the French national ethical committee. The study received funding in February 2020. As of October 2020 (submission date), and due to the context of the COVID-19 pandemic, a total of 10 participants out of 50 had been enrolled in the study. The projected date for the end of the data collection is December 2021. Data analyses have not been started yet, and publication of the results is expected for Spring 2022.

**Conclusions:**

The effects of psychomotor rehabilitation using the Medimoov exergame platform on the risk and fear of falls will be evaluated. This pilot study will be the basis for larger trials.

**Trial Registration:**

ClinicalTrials.gov NCT04134988; https://clinicaltrials.gov/ct2/show/NCT04134988

**International Registered Report Identifier (IRRID):**

DERR1-10.2196/24665

## Introduction

The ageing population has a higher risk of developing sensory, physical, mental, and cognitive disorders, which increase their risk of falls [1,2]. Physical disability is highly prevalent in older adults and encompasses mobility and balance impairment. Cognitive alterations also induce walking difficulties, leading to increased risk of falls [2,3]. Each year, 20% to 30% of older adults fall [1]. Of these, 25% to 50% will relapse within the year, which aggravates the problem by the multiplication of injuries [1]. Falls lead to numerous and serious health consequences, loss of independence, and institutionalization [1,4]. In addition, falls and balance impairment may induce fear of falling, which may lead to social isolation, anxiety, and depression as well as decreased mobility, physical disability, and falls [5,6]. Fear of falling encompasses fall-related fear, fall-related self-efficacy, and balance confidence [7]. In community-dwelling older adults (≥75 years old), 41.5% experience fear of falling. In long-term care, this prevalence is higher: 63% of institutionalized older adults express a fear of falling. A recent literature review shows that community-dwelling older adults (≥65 years old) score an average of 15 on the Short Fall Efficacy Scale–International (Short FES-I), which measures the fear of falling; this score indicates a moderate fear of falling [8].

Fall prevention programs can reduce the risk of falls if they combine different exercise categories [9,10]. The literature review of Vieira et al (2016) [3] and the quasi-experimental study of Pereira et al (2014) [10] with 506 community-dwelling older adults demonstrate that benefiting from regular physical activities is associated with an improvement in physical abilities and balance. The systematic review and meta-analysis of Tricco et al (2017) [9], which included 54 studies and 41,596 participants, confirmed these results and added that exercise combined with vision assessment and treatment as well as environmental modification are effective in fall prevention [9]. In addition, fall prevention programs should target cognitive function improvement [2]. Cerebral plasticity and cognitive functions are essential for motion and balance [2]. Among executive functions, inhibition is particularly relevant to fall prevention because poorer results of response inhibition tests are associated with future risk of falls [11]. Cognitive inhibition suppresses irrelevant information from the working memory and facilitates automatic response, which may explain its importance for preventing the risk of falls, especially during mobility tasks involving distraction (eg, walking outside) [11]. Adapting the rehabilitation to the patient’s cognitive status is paramount to prevent falls [12] and to allow older adults to focus on their rehabilitation programs. Psychomotor therapists are among the professionals recommended by the Haute Autorité de Santé, the French national health agency, to safely administer physical exercise programs to older adults [13]. These therapists possess skills and expertise in intervening in the psychomotor dimensions of falls, namely, the motor, sensory, and cognitive aspects [14].

In rehabilitation, exergames are increasingly being studied, especially exergames using Kinect sensors (Microsoft Corporation) [15-18]. According to Tanaka et al [18], “exergaming platforms are designed to track body motion or body reactions and provide both fun and exercise for game players.” Several exergames have been designed for the rehabilitation of older adults, and some of them were found to be effective in studies with before-and-after designs or randomized controlled trials [19,20]. Their safety was deemed good: no adverse effects related to their use were identified [21]. We did not find any studies that compared the effects of patient-personalized exergame-assisted rehabilitation with those of traditional rehabilitation programs [21]. Studies should explore not only the efficacy of an exergame-assisted rehabilitation program, but also its acceptability [21]. Adherence to and engagement in a rehabilitation program are at the heart of its effectiveness and therefore should be considered when evaluating the exercise rehabilitation program [21]. There is no consensus in the literature regarding the adherence of older individuals to rehabilitation programs with exergames compared to programs without exergames [21]. However, some experimental studies with older adults have shown better adherence in a rehabilitation group with exergames than in the control group [22,23]. Exergames are considered to be enjoyable and have the potential to increase motivation and reduce fear of falling. Therefore, they are of particular interest in engaging older people who are afraid of falls in exercise programs.

Medimoov (NaturalPad) [24] is a movement-based video game for rehabilitation of older adults that allows the therapist to choose the movements the patient will perform to interact with the game. The difficulty and the speed of the game can be defined by the therapist, allowing for a fine-tuned personalization of the sessions according to the patient’s progress. A preliminary study showed that using Medimoov’s personalized activities may positively influence older adults’ functional ability and motivation [15]. Most existing studies evaluating the use of exergames do not involve an appropriate control group (ie, a control group following the standard rehabilitation program) [17,21] or do not involve an exergame specifically designed for rehabilitation of older adults that allows for the personalization of the sessions [21,22,25]. Thus, this study aims to evaluate the effects of Medimoov on older adults with fear of falling compared with standard psychomotor rehabilitation as prescribed by physicians. Two aspects of the rehabilitation will be explored: the preventive function (decreased risk of falls) and the therapeutic function (decrease of fear of falling and increase of motivation during rehabilitation).

The main objective is to evaluate the efficacy of exergames played on the Medimoov platform on fear of falling and risk of falls. The secondary objective is to assess the effect of the exergame intervention on the participants’ executive functions during the study. Another secondary objective is to explore the perception of exergame-assisted rehabilitation by the participants of the intervention group. The hypothesis is that exergames in rehabilitation can lead to decreased fear of falling and risk of falls due to an improvement of balance, physical functions, and executive functions, including an improvement in cognitive inhibition.

## Methods

### Design

This study is an open, randomized controlled study in parallel groups with blind data collection for the evaluation criteria. The protocol follows the SPIRIT (Standard Protocol Items: Recommendations for Interventional Trials) guidelines [26,27].

### Participants and Recruitment

The research project will be conducted in two intermediate-care wards for older adults at the Charles Foix Hospital, a French geriatric hospital. Guidelines to calculate the sample size do not exist in the literature yet; thus, the sample size has been estimated based on previous studies evaluating fear of falling–focused interventions [28,29]. A sample size of 20 participants per group is often reported. A total of 25 participants per group will be recruited to factor in a potential 20% withdrawal or other variations. Recruitment will be conducted among hospitalized patients in intermediate-care rehabilitation hospital wards. The inclusion criteria will be as follows: (1) age of 65 years or older, (2) ability to understand and answer short and simple questions (as determined by the clinical interview), (3) ability to stand upright in a bipedal position, feet together, for longer than 1 minute with or without a technical aid, (4) a score of 13 or greater on the FES-I [30] (moderate or severe fear of falling), (5) stable medical condition, and (6) ability to give written consent. The exclusion criteria will be as follows: (1) cannot correctly distinguish the elements on the screen, (2) in palliative care, (3) under a legal protection measure, (4) obtained a score <16 on the Mini Mental State Examination (MMSE) [31], and (5) recently underwent orthopedic surgery (<2 months); the latter is an exclusion criterion because it requires specific rehabilitation programs [32]. The MMSE will be used for screening purposes only to exclude patients with severe cognitive disorders that would prevent them from participating. Participation may be interrupted at the participant’s request or if the participant experiences an adverse health event (eg, stroke). All patients hospitalized in the rehabilitation ward at the beginning of the study will be screened for eligibility by their physicians, and if eligible, will be asked to participate after a detailed presentation of the protocol by a postdoctoral fellow or a research professional. The eligibility of the patients admitted to hospital after the start of the study will be verified. Participant recruitment will be ongoing until the sample number (N=50) is reached. Eligible patients will receive a letter of information. A random selection will be conducted if the number of eligible patients is higher than the number of required participants.

### Randomization

After the randomization, patients will be allocated to an intervention group (rehabilitation program with the Medimoov platform) or to a control group (traditional psychomotor therapy sessions). The randomization will be conducted directly after the signature of the consent form. To ensure concealed allocation [33], each participant will be assigned a code used for the randomization. As the participants will not all be identified before the randomization, block randomization will be conducted (rather than stratification) to control the sample size of each group using the “blockrand” function of RStudio software (RStudio PBC).

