#### The TUAG test

This test [40] consists of standing up from a chair with armrests, walking 3 meters, turning around, and coming back to sit. The test lasts less than 5 minutes. A shorter time of execution of the test indicates a better balance and stability and a lower risk of falls; the time of execution is thus analyzed as a quantitative value indicating the risk of falls. Risk of falls is identified if the duration of the test is longer than 20 seconds. The 2-week test-retest fidelity, measured by an intraclass correlation coefficient (*r*), ranges between 0.93 and 0.99 [40]. Compared to other assessment tools for risk of falls, such as the One-Leg Stand test, the Functional Reach test, and the Tinetti test, the TUAG has demonstrated better discriminant validity for fall prediction [40]. When compared to the Berg Balance Scale and the Tinetti test, the TUAG test has demonstrated the best sensitivity to change (93%) [41]. It has also demonstrated a higher participation rate than the One-Leg Stand test and the Functional Reach test [40]. For these reasons, it has been chosen as the primary outcome for this study.

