### Study Procedures

Three assessments will be performed by a psychomotor therapist (who is not one of the therapists involved in the rehabilitation program) focusing on physical and cognitive capacities. The first assessment will be performed during the first week, before the start of the rehabilitation program; the second will occur during week 4; and the third will occur during week 8, at the end of the rehabilitation program. Assessments will be blinded; the assessors will not know the assigned group of each participant. To preserve neutrality, assessments will be performed in a different room than the sessions.

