#### Endpoints

The primary clinical endpoint is the comparison of the changes in FES-I scores between the two groups. The main secondary endpoint is the comparison of changes in TUAG scores between the groups. Other secondary endpoints are a significantly greater improvement in the One-Leg Stand test, the SPPB test, the Trail Making Test Parts A and B, and the Stroop test in the intervention group and a high level of satisfaction in the intervention group.

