### Strengths and Limitations

One of the strengths of the study is that it follows the SPIRIT guidelines [26,27] and the PEDro recommendations [33]. It ensures internal and external validity and provides the necessary information to interpret the results of this study. Another strength is the comparison to the standard in rehabilitation for fall prevention in the context of French geriatric hospitals. Regarding outcome measurement, standardized measures have been chosen based on their sensitivity to change [40] to highlight the effect of the intervention. Moreover, results regarding the intervention effectiveness are assessed with standardized scales and with accelerometers, ensuring data triangulation.

This protocol also presents some limitations. Due to the nature of the intervention, double blinding is not possible. However, measures of the outcomes will be blinded and performed by trained assessors to minimize bias. Moreover, stratification on age, gender, fear of falling, and risk of falls will not be possible for the randomization, as the participants will not all be identified at the beginning of the study. However, possible differences between groups at baseline will be tested to consider them in data interpretation. Desirability bias can occur with participants trying to please the assessor. This bias will be the same in both groups. To minimize this bias, primary and secondary outcomes will be assessed by an independent assessor (different from the psychomotor therapist administrating the intervention). This is an exploratory study with significant limitations in terms of sample size, power, and hence, depth of the statistical analysis that can be conducted. However, in the context of a future larger trial (if warranted), an appropriate sample size and power calculation will be undertaken, which would also allow for a more detailed and robust statistical analysis of the data with enhanced validity and integrity of the results.

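### Randomisation comes before the first assessment in an open trial, so knowledge of the arm could alter the baseline of the participant-rated FES-I

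*Protocol article*

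**What the plan says.** Four parts of the protocol article bear on this.

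- **Order of events.** Under Randomization: "The randomization will be conducted directly after the signature of the consent form". Under Study Procedures: "The first assessment will be performed during the first week, before the start of the rehabilitation program". Table 1 agrees, with allocation in an earlier column than the first assessments.
- **Blinding.** The Design section describes an "open, randomized controlled study in parallel groups with blind data collection". Strengths and Limitations adds: "Due to the nature of the intervention, double blinding is not possible". Blinding applies to the assessors: "Assessments will be blinded; the assessors will not know the assigned group of each participant".
- **Primary endpoint.** The Endpoints section states: "The primary clinical endpoint is the comparison of the changes in FES-I scores between the two groups". The section on the TUAG test says of TUAG: "For these reasons, it has been chosen as the primary outcome for this study". The two sections disagree.
- **Analysis.** Statistical Analysis compares pre-to-post differences between groups by t test or Mann-Whitney test. No adjustment for baseline is mentioned.

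Inclusion criterion 4 requires an FES-I score of at least 13, so a score exists before randomisation. Table 1 nevertheless lists a separate week-1 score, and nothing says that the screening score serves as baseline.

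**The concern.** Randomisation makes the groups comparable at the moment of allocation. A baseline taken before that moment cannot be affected by the arm. One taken afterwards can be, if the person supplying the value knows the arm. The FES-I is a questionnaire in which participants rate their own concern about falling, so the unblinded participant is the source of the data. A blinded assessor in a separate room does not change that.

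Because the endpoint is a change, the baseline is subtracted from the outcome, and any effect of allocation on it goes straight into the treatment comparison. The protocol also plans to test for baseline differences and consider them in interpretation. With a baseline taken after allocation, that test cannot separate chance imbalance from a reaction to the assignment.

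**Working it through.** **1. The plan's own figure.** There is no power calculation to reproduce. The dropout inflation is right: 20 / (1 − 0.20) = 25 per group. The proposed fix does not alter it.

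**2. Sequence.** Randomization and Study Procedures together give consent, randomisation, first assessment, session 1. Table 1 shows the same order, but the conclusion does not depend on it. No section describes withholding the allocation from participants until the first assessment is complete.

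**3. How a shift enters the endpoint.** Read the endpoint as change from the first assessment to week 8. Let knowing the arm move the week-1 score in one arm by b points, and let a fraction p of that shift remain at week 8.

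- Observed week-1 score in that arm = true score + b
- Observed week-8 score in that arm = true score + p·b
- Bias in the between-group change = p·b − b = −(1 − p)·b

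With p = 0 the bias is the full b points. With p = 1 it cancels. If b is positive in the exergame arm (more fear reported at week 1), that arm appears to improve more. If b is negative, a real benefit is masked.

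**4. Illustration of scale.** From the document: 25 per group (20 after 20% withdrawal), and a 4-week test-retest coefficient of 0.83 for the FES-I, used here as the pre-post correlation r. Assumed, because the document gives no values: SD of the score 4, 5 or 6 points on the 7 to 28 scale; b of 0.5, 1 or 2 points; p = 0; two-sided 5% test; no true effect.

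- SD of change = SD × √(2(1 − r))
- Standard error of the contrast = SD of change × √(2/n)
- Type I error ≈ 1 − Φ(1.96 − b/SE) + Φ(−1.96 − b/SE)

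For SD = 5, r = 0.83, n = 25, b = 1: SD of change = 5 × √0.34 = 2.92; SE = 2.92 × √0.08 = 0.82; b/SE = 1.21; type I error = 22.8%.

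| n per group | r | b (points) | SD 4 | SD 5 | SD 6 |
|---|---|---|---|---|---|
| 25 | 0.83 | 0.5 | 11.8% | 9.3% | 8.0% |
| 25 | 0.83 | 1 | 32.9% | 22.8% | 17.3% |
| 25 | 0.83 | 2 | 85.8% | 67.9% | 52.4% |
| 25 | 0.5 | 1 | 14.3% | 10.9% | 9.1% |
| 20 | 0.83 | 1 | 27.3% | 19.2% | 14.8% |

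**5. Would covariate adjustment help?** Only in part. With equal variances, adjusting for the affected baseline leaves a bias of r·b, which is 0.83 points for b = 1 and r = 0.83.

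**6. After the fix.** If the first assessment is recorded before the participant can know the arm, b = 0 and this source of bias disappears.

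**The case against.** The strongest objection is that disclosure is inferred. The protocol says when randomisation is carried out, not when a participant learns the result, and an article may leave that detail to the full protocol. If participants are told only after the week-1 assessment, the risk is gone. This stands as a limit on the conclusion: the order is documented, the bias is not. It does not remove the point, because the text as written permits early disclosure in an open trial and describes no safeguard against it.

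A reader might also infer that people assigned to the exergame would be more afraid at week 1 because they expect demanding standing play. The programme descriptions do not support this. Both arms work seated through session 8 and begin standing work at session 9, the exergame arm is systematically offered a harness, and both arms receive 16 sessions of 35 minutes. Nothing in the document points to a shift in a particular direction.

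The protocol argues that desirability bias will be equal in both groups. That concerns pleasing the assessor, and does not cover a first answer given in knowledge of the arm.

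Two further points stand as qualifications. If TUAG is the primary outcome, the exposure is smaller, since a timed test is less open to expectation, though it still depends on effort. The authors also call the study exploratory and limited in power. That lowers the weight of any single test, but it is no reason to keep an avoidable route to bias.

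**Conclusion.** The point holds as a weakness in the order of events. The baseline is measured after randomisation, in participants who are not blinded, and the endpoint that the Endpoints section calls primary subtracts that baseline. Any week-1 shift specific to one arm that has faded by week 8 passes in full into the between-group change.

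The documents do not support the stronger statement that the baseline will be biased, or biased in favour of the exergame. The time of disclosure is not stated, both arms are active, and the size and direction of any shift are unknown. The type I error figures show only how sensitive a trial of this size would be: at 25 per group and r = 0.83, a 1-point shift gives 17% to 33%, on an assumed SD, shift, alpha and complete fading by week 8. With r = 0.5 the range is 9% to 14%. The change is worth making because it is nearly free and closes the route altogether.

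**What to change.** Change the order to consent, first assessment, then randomisation. If randomisation must stay next to consent, release the allocation to participant and staff only once the first assessment is recorded, and before session 1. Correct the Randomization section and Table 1 to match. If disclosure already works this way, one sentence saying so is enough.

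The cost is that randomisation, or its disclosure, happens a few days later. The first assessment already precedes session 1, so no visit, staff time or measurement is added, and the sample size stays at 25 per group.

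For participants already enrolled under the current order (10 of 50 at submission), keep the week-1 score as baseline so that the endpoint has one definition. Where a screening FES-I was recorded before randomisation, use it only in a sensitivity analysis. Selection at 13 or more brings regression to the mean, expected to be equal in both arms. Screening is done by the patients' physicians and the study assessments by an independent therapist, so the two scores may also differ in how they were obtained.

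The Endpoints and TUAG sections should be reconciled at the same time, since the weight of this point depends on which outcome is primary.
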